# Pragmatic, open-label, multicentre, randomised controlled trial to guide initial therapy for immune checkpoint inhibitor-induced inflammatory arthritis comparing standard of care (prednisolone) to adalimumab without glucocorticoids: REACT trial protocol

**DOI:** 10.1136/bmjopen-2026-116847

**Published:** 2026-03-03

**Keywords:** Clinical Trial, Drug Therapy, IMMUNOLOGY, RHEUMATOLOGY, ONCOLOGY

## Abstract

**Introduction:**

Immune checkpoint inhibitors (ICIs) have revolutionised cancer treatment through targeted disruption of the physiological pathways that maintain tissue tolerance, but which are co-opted by cancers to evade immunosurveillance. Thus, the resultant T-cell activity often causes immune-related adverse events including immune checkpoint inhibitor-induced inflammatory arthritis (ICI-IA). ICI-IA results in functional impairment that frequently persists, even after ICI discontinuation, with substantial quality-of-life impacts for cancer survivors.

A high-quality body of evidence to guide ICI-IA management remains an unmet need. Pharmacological treatment may be prolonged, typically begins with non-specific immunosuppression, including systemic steroids, and is usually only rationalised to more targeted therapy in resistant cases. Moreover, retrospective data suggest the high dose glucocorticoids sometimes used in new-onset ICI-IA may be associated with worse cancer outcomes.

Tumour necrosis factor (TNF) inhibition strategies are well established with excellent efficacy and safety profiles in ‘spontaneous’ inflammatory arthritides including rheumatoid and psoriatic arthritis. Mechanistic evidence from ex vivo and murine studies also supports the utility of anti-TNF therapy for steroid-refractory cases of ICI-IA. Although good clinical responses have been reported in this setting, the REACT trial (REmission induction of Arthritis caused by Cancer ImmunoTherapy) aims to provide randomised and robust clinical evidence for deploying targeted therapy earlier in ICI-IA management. It will test whether up-front anti-TNF therapy can more effectively and quickly control symptoms, reduce glucocorticoid exposure, prevent early ICI discontinuation and increase the frequency of drug-free ICI-IA remission.

**Methods and analysis:**

REACT is a prospective, multicentre, open-label, superiority, two-arm, randomised controlled clinical trial to guide initial therapy for patients with ICI-IA. The trial will compare the current standard of care (initial prednisolone; Arm A) with the anti-TNF drug, adalimumab without glucocorticoids (Arm B).

The primary outcome is glucocorticoid-free arthritis remission rate at 24 weeks where remission is defined as: (i) No use of systemic or intra-articular glucocorticoids (except when used for adrenal insufficiency) within 4 weeks prior to assessment at 24 weeks; and (ii) absence of synovitis on clinical examination.

**Ethics and dissemination:**

The protocol was approved by East Midlands—Leicester South Research Ethics Committee on 31-Oct-2024 (Ref: 24/EM/0202). Participants are required to provide written informed consent. The results of this trial will be disseminated through national and international presentations and peer-reviewed publications.

**Trial registration number:**

ISRCTN18217497.

STRENGTHS AND LIMITATIONS OF THIS STUDYREACT tests the most widely used anti-TNF agent in the UK, adalimumab, which has the convenience of subcutaneous administration.Adalimumab is being used without glucocorticoids, avoiding unnecessary over-immunosuppression.The lack of placebo reduces burden, complexity and cost of the trial.REACT has been co-developed with patient partners who co-designed the patient-centred ranked composite outcome that will be used as an exploratory outcome.REACT does not use loading doses of adalimumab, which have been shown to reach steady state drug levels more quickly and more rapidly control inflammation.

## Introduction

 Immune checkpoint inhibitors (ICIs) have revolutionised cancer treatment through targeted disruption of the physiological pathways that maintain tissue tolerance, but which are co-opted by cancers to evade immunosurveillance. However, the heightened T cell activity that results also causes immune-related adverse events (IrAEs).^1^,^3^ Immune checkpoint inhibitor-induced inflammatory arthritis (ICI-IA) occurs in 5–7% of treated patients.^2^ The indications for ICI therapy are rapidly increasing (projected compound annual growth rate is 28% in the European market between 2025–2033^4^). ICI-IA is currently quite a common problem in rheumatology clinics and will continue to increase.

ICI-IA results in functional impairment,^5^ which is often persistent, even after ICI discontinuation,^6^ and carries a large emotional and quality of life impact for patients.^7^ However, there is no high-quality body of evidence to guide treatment, with current recommendations not evidence based.^8^,^10^ Management may start with intra-articular glucocorticoid injections in mild cases, but when systemic immunosuppression is required, the current first-line therapy is glucocorticoids. Moderate glucocorticoid doses are inadequate for inducing drug or steroid-free remission in many patients with ICI-IA; however, higher doses (≥60 mg/day prednisolone) are associated with poorer oncological outcomes.^11^ Failure to control ICI-IA with glucocorticoids leads to the introduction of disease-modifying anti-rheumatic drugs (DMARDs), such as methotrexate or leflunomide, followed by biological DMARDs such as anti-tumour necrosis factor (TNF) or anti-interleukin-6 (IL-6) therapy. This treatment sequencing approach is associated with prolonged immunosuppression and may contribute to persistence,^6 12^ since data from other forms of inflammatory arthritis suggest a ‘window of opportunity’ in very early disease during which effective therapy results in milder disease or remission.^13 14^

TNF inhibition has shown efficacy in refractory ICI-IA,^2 15 16^ consistent with high TNF expression in synovial biopsy tissue.^17^ Anti-TNF agents are very well-tolerated with a good safety profile and proven efficacy in rheumatoid arthritis (RA) and psoriatic arthritis (PsA). Emerging data from ICI-IA synovial fluid show the presence of clonally expanded effector CD8+ T-cell populations that are highly productive of TNF^5^ and likely recruited by an activated myeloid population also involving TNF.^18^ Infiltrating CD8+ T-cell numbers within melanoma correlate with response to ICI but are reduced by TNF.^19^,^21^ Thus, TNF may provide a tumour escape mechanism in the context of ICI therapy. Indeed, in humanised mice, ICI treatment alone can induce inflammatory arthritis associated with TNF-producing T cells, against which anti-TNF therapy is efficacious.^22^ The ability of anti-TNF given in combination with ICI to improve ICI cancer outcomes has been tested in a phase 1b clinical trial and found no adverse safety signal.^23 24^ Together, these data make TNF an attractive target in ICI-IA.

Therefore, the REACT trial (REmission induction of Arthritis caused by Cancer ImmunoTherapy) has been designed in answer to recent calls for a paradigm shift^11 25 26^; it aims to test whether earlier use of more targeted therapies, specifically anti-TNF instead of glucocorticoids, will lead to more effective and rapid symptom control from ICI-IA, reduce glucocorticoid exposure, prevent early ICI discontinuation and increase the frequency of drug-free ICI-IA remission. Data on cancer outcomes will also be collected.

## Methods and analysis

### Patient and public involvement

A patient group with lived experience of ICI-IA helped shape the proposal that was submitted for funding through discussion of key questions. They contributed to the trial design (current standard of care vs anti-TNF alone) choosing this over other options including standard of care plus anti-TNF or placebo; the consideration to not over-immunosuppress patients was thought to be important for patient acceptability. Visit burden and acceptability of ultrasound-guided biopsy were also discussed.

A patient partner was a co-applicant during funding acquisition with both the trial management group (TMG) and trial steering committee (TSC) each having at least one patient partner as a member.

Patient partners were also involved in trial protocol finalisation, in particular, playing a key role in the development of a patient-centred composite outcome measure, itself used as an exploratory outcome for REACT (see Discussion). Details on the development of this will be published separately.

Patients have and will continue to review the patient information sheet and consent forms. Patient partners will also continue to contribute to newsletters, lay summary results and infographics and publicity about the trial; they will also help disseminate results of the trial via patient networks and public events.

### Trial design

REACT is a prospective, multicentre, open-label, superiority, two-arm, randomised controlled clinical trial to guide initial therapy for patients with ICI-IA. The trial will compare the current standard of care (prednisolone; Arm A) to adalimumab without glucocorticoids (Arm B) (figure 1). REACT aims to recruit 70 patients (35 in each arm) from >10 UK hospitals.

**Figure 1 F1:**
[figure not shown]
Schema for REACT trial. *Screening visit and Week 0 can be conducted on the same day. REACT, REmission induction of Arthritis caused by Cancer ImmunoTherapy.

During the 48-week treatment period, participants have regular contact with the participating clinical and research teams either in person or via the telephone, according to the patient pathway (online supplemental appendix 1).

The WHO Trial Registration Data Set is included in online supplemental appendix 2.

The full protocol can be requested from the REACT Trial Office ([contact]).

### Consent

Written informed consent is obtained by the investigator (or an appropriately trained and suitably delegated sub-investigator, who must be a Specialist Trainee level doctor or above). A patient information sheet is provided to facilitate this process (online supplemental appendix 3). If the patient agrees to participate, an informed consent form must be signed when the patient attends their first clinic appointment, prior to their entry onto the trial (online supplemental appendix 4).

### Randomisation

Participants are randomised 1:1 to receive either standard of care (prednisolone; Arm A) or adalimumab without glucocorticoids (Arm B) by the investigator or suitably trained delegate. Randomisation will be performed via a computer programme developed by the Cancer Research UK Clinical Trials Unit (CRCTU). The personnel randomising participants will not have access to the random allocation sequence. To avoid any possibility of the treatment allocation becoming too predictable, a 20% random element has been included in the randomisation algorithm. Stratification variables are tumour type (melanoma or non-melanoma); ICI agents used (single or combination); planned initial prednisolone dose (20 mg or 40 mg); duration of symptoms (≤12 weeks or >12 weeks); and participation in the optional biopsy sub-study.

### Patient selection

Patients are identified through clinics, multi-disciplinary teams and the acute oncology service. Oncologists identifying a potential participant will refer for rheumatology assessment at a participating hospital who will then consent the patient prior to confirming eligibility and subsequent randomisation.

Box 1 contains the key eligibility criteria.

Box 1Eligibility criteria for the REACT trialInclusion criteriaInformed consent must be obtained prior to any trial-related procedures being performed.Able to understand and comply with the requirements of the trial.Inflammatory arthritis with at least one clinically swollen joint at screening.Male and female participants aged ≥18 years.Patient treated with immune checkpoint inhibitor (ICI) concurrent with or last dose within 12 weeks prior to the onset of inflammatory arthritis.Decision of two treating physicians, one of whom must have expertise in the management of inflammatory arthritis, that treatment with systemic glucocorticoids would be appropriate management for their inflammatory arthritis. Details of the physicians who have decided this will be documented in the source data.Exclusion criteriaIf currently using oral glucocorticoids, use must not exceed 2 weeks prior to baseline (except hydrocortisone for adrenal replacement where longer term use is allowed).Pre-existing (prior to first use of ICI) inflammatory arthritis due to rheumatic autoimmune disease.The arthritis not considered, by the treating physician, to be immune checkpoint inhibitor-induced inflammatory arthritis (ICI-IA).Active or latent tuberculosis (TB) (unless having fulfilled chemoprophylaxis management according to local guidelines) or other chronic infection considered a contraindication to anti-TNF.Positive test for HIV, Hepatitis C (HCV) (evidenced by both positive anti-HCV antibody and HCV-RNA in serum), Hepatitis B Virus (HBV) as evidenced by positive hepatitis B surface antigen (HBsAg) or anti-hepatitis B core antibodies (HBcAb). Participants with a negative result in the last 6 months will be eligible.History of demyelinating disorder.Hypersensitivity to the active substance or to any of the excipients in the adalimumab preparation.Any medical, surgical or psychiatric condition that the investigator believes may jeopardise the participant, or the validity of the trial results, were they to participate in the trial.Moderate to severe heart failure (New York Heart Association III/IV).Concurrent use of other biological immunosuppressive drugs or Janus kinase inhibitors.Live vaccine received less than 4 weeks before first dose of trial drug.Any current severe infection.Known ocular herpes simplex.REACT, REmission induction of Arthritis caused by Cancer ImmunoTherapy.

### Interventions and dose modifications

#### Arm A—standard of care

The comparator will follow usual care for this patient population. A reducing course of oral prednisolone with a starting dose of 20 mg/day or 40 mg/day decided prior to randomisation on clinical grounds by the treating rheumatologist.

Guidance on tapering and management in case of non-response or relapse on prednisolone withdrawal is provided in online supplemental appendix 5.

If arthritis fails to remit, further therapy may be provided according to clinical practice and American Society of Clinical Oncology (ASCO) recommendations.^8^ This may include further oral prednisolone with or without oral DMARDs such as methotrexate, leflunomide or hydroxychloroquine, titrating up to a biological DMARD (anti-TNF or anti-IL6R) if required. We recommend avoiding sulfasalazine given the experience of hypersensitivity reactions in this context.^10 27 28^ With disease control, therapy will be titrated down to the minimum amount required to control synovitis if drug cessation is not possible.

#### Arm B—adalimumab without glucocorticoids

Adalimumab 40 mg every other week by subcutaneous injection. Participants will be taught how to self-administer by the trial investigators.

Investigators may stop adalimumab at Week 24 or after, provided there has been evidence of sustained remission defined as the absence of synovitis on clinical examination on at least two consecutive occasions 4 weeks apart. If synovitis recurs following this, then adalimumab can be restarted. With inadequate response at Week 12 or after, the dose of adalimumab can be increased to 80 mg every other week (online supplemental appendix 5).

If arthritis fails to remit, then further therapy may be required in addition to adalimumab, or in place of adalimumab if the participant does not respond. Further therapy may include oral prednisolone, oral DMARDs or an alternative biological DMARD. With disease control, therapy will be titrated down to the minimum amount required to suppress synovitis if drug cessation is not possible, although adalimumab will not be stopped before Week 24 except in the event of non-response or toxicity.

### Treatment compliance

Drug accountability logs are not required for prednisolone. The local trial pharmacist is responsible for maintaining and updating drug accountability logs for adalimumab to monitor compliance. In addition, participants will be issued with a diary to complete each day, recording the dosage of medication and whether any doses were missed. The diary also includes a section where participants can record any relevant information such as side effects suffered or reasons for missed doses. The completed diary will be collected by the site at each protocol scheduled visit and checked.

### Concomitant medication

#### Arm A—standard of care

Use of biological DMARDs such as TNF or IL-6R inhibitors is prohibited in the first 12 weeks after baseline and their use within this period would result in the participant being considered a non-responder.

#### Arm B—adalimumab without glucocorticoids

If taking glucocorticoids at screening (other than for adrenal insufficiency), use must not exceed 2 weeks prior to the baseline visit with an aim to discontinue use at baseline on first administration of adalimumab. However, further glucocorticoids may be used in this arm if clinically indicated. Use of other biological DMARDs (eg, anakinra and abatacept) or other TNF-antagonists is not recommended concomitant with adalimumab based on the possible increased risk for infections, including serious infections and other potential pharmacological interactions.

#### Both arms

Co-treatment with Cytochrome P450, family 3, subfamily A (CYP3A) inhibitors, including cobicistat-containing products, is expected to increase the risk of systemic side-effects with prednisolone and should be monitored and managed as per standard practice by the investigator.

Live vaccines should be avoided while the participant is on active treatment within the trial.

### Trial outcomes

The primary outcome is glucocorticoid-free arthritis remission rate at 24 weeks where remission is defined as: (i) No use of systemic or intra-articular glucocorticoids (except when used for adrenal insufficiency) within 4 weeks prior to assessment at 24 weeks; and (ii) absence of synovitis on clinical examination.

Key secondary outcomes include time to arthritis remission, drug-free arthritis remission at 48 weeks, 66/68 swollen and tender joint counts, patient acceptable symptom state, cumulative glucocorticoid exposure, other IrAEs, health-related quality of life, cancer response and overall survival. The full list of secondary and exploratory outcomes is listed in online supplemental appendix 6.

Where an Investigator removes a participant from the trial or if the participant declines further participation, final Week 24 or Week 48 assessments will still be performed, if possible, as long as consent is not withdrawn. If a participant ceases trial treatment due to adverse clinical or laboratory events, they will be treated and monitored according to accepted medical practice and continue to attend the remaining trial visits if they agree.

### Statistical analysis plan

A formal statistical analysis plan (SAP) for REACT provides a detailed description of the planned analyses and can be requested from the REACT Trial Office ([contact]). Unless reported otherwise, the threshold for determining statistical significance from hypothesis testing is p<0.05. Where a parametric and non-parametric test has been specified dependent on the normality of data distribution, this will be assessed using a q-q plot, or a Shapiro-Wilk test where p<0.05 will be considered to indicate data is non-normally distributed. A brief outline of planned analyses has been included.

#### Outcome analyses

The safety population will include all patients who receive any trial treatment.

The modified intention-to-treat population for the primary analyses will include all patients who receive any trial treatment and who have a baseline joint assessment measurement and at least one further joint assessment post-baseline. No imputation of the primary outcome is planned for patients missing a 24-week assessment; instead, the trial sample size has been inflated to account for patient withdrawal. For the secondary endpoints, this includes all patients who receive any trial treatment and have available data for the respective outcome measure.

The intention-to-treat population includes all randomised patients in their treatment arms who have available data for the respective outcome measure.

Glucocorticoid-free arthritis remission rate at 24 weeks will be calculated for each treatment arm by dividing the number of patients reaching the response criteria by the total number of patients randomised to each arm. Failures in glucocorticoid-free arthritis remission recorded prior to the 24-week outcome (eg, due to early initiation of biological DMARD trial) will be used in this assessment. Where patients are missing the primary outcome (eg, because their Week 24 assessment is missing), they shall be treated as a failure and included in the denominator only. In addition, the number of such patients in each arm will be reported. 95% CIs will be calculated for each rate.

The remission rate will be compared between arms using a χ^2^ or Fisher’s exact test. Moreover, we will use logistic regression models, adjusted for stratification variables and other baseline covariates deemed to be associated with the outcome (such as patient standard of care). This will allow us to present the treatment effect for each of the stratification variables, as well as attempt to distinguish efficacy effects relating to standard of care compared with those because of trial treatment.

Analyses of secondary and exploratory measures are included in online supplemental appendix 7.

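### The protocol article gives incompatible populations, denominators and missing-data rules for the primary endpoint, so the same data can yield different primary results

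*Protocol article*

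**What the plan says.** The primary endpoint is binary: glucocorticoid-free arthritis remission at 24 weeks (Trial outcomes). The Outcome analyses section then says four things about who is analysed and how missing outcomes are handled.

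- **Population.** "The modified intention-to-treat population for the primary analyses will include all patients who receive any trial treatment and who have a baseline joint assessment measurement", with at least one later joint assessment also required.
- **Missing week 24, first rule.** "No imputation of the primary outcome is planned for patients missing a 24-week assessment; instead, the trial sample size has been inflated" to account for withdrawal.
- **Denominator.** The rate is obtained by "dividing the number of patients reaching the response criteria by the total number of patients randomised to each arm".
- **Missing week 24, second rule.** Where the primary outcome is missing, "they shall be treated as a failure and included in the denominator only", and the number of such patients is reported by arm. Failures already recorded before week 24 are carried into the assessment.

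The section also defines a third set: "The intention-to-treat population includes all randomised patients in their treatment arms who have available data for the respective outcome measure".

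The Sample size calculation section takes 21% v 55%, 80% power and a 5% significance level, arrives at 62 patients, and adds a 10% dropout allowance to reach 70 (35 per arm).

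**The concern.** There are two separate conflicts.

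The first is the missing-data rule. Scoring a missing outcome as failure is a single imputation, so it cannot stand beside a statement that nothing is imputed. Enlarging the sample replaces imputation only if the patients concerned drop out of the analysis.

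The second is the denominator. A patient who is randomised but never treated, or who has no joint assessment after baseline, is outside the modified intention-to-treat set but inside the total randomised. The intention-to-treat set, limited to those with available data, is a third possible denominator.

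At stake is the primary result of a trial with 35 patients per arm, where a few patients can move the estimate by several percentage points. A reader of the article cannot tell which result was prespecified. If the modified intention-to-treat reading governs, it also removes patients for reasons arising after randomisation (not starting treatment, not returning). In an open-label trial those reasons could differ by arm.

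**Working it through.** **Step 1. The plan's own sample size.** Inputs from Sample size calculation: p1 = 0.21, p2 = 0.55, power 80%, alpha 5%. Sidedness is not stated; two-sided reproduces the figure. With p̄ = (0.21 + 0.55)/2 = 0.38:

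n per arm = [1.960·√(2·0.38·0.62) + 0.842·√(0.21·0.79 + 0.55·0.45)]² / 0.34² = 30.8, so 31 per arm and 62 in total.

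Dropout: 62/0.90 = 68.9, so 69, rounded to an even 70. Both stated figures reproduce.

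**Step 2. Which missing-data rule does that calculation fit?** Assume 10% missing in each arm, independent of outcome, and that 21% and 55% are rates among assessed patients.

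- Missing excluded: 35 × 0.90 = 31.5 per arm, rates unchanged. Power = Φ{[0.34·√31.5 − 1.960·√(2·0.38·0.62)] / √(0.21·0.79 + 0.55·0.45)} = 80.9%.
- Missing counted as failure: 35 per arm, rates 0.21 × 0.90 = 18.9% and 0.55 × 0.90 = 49.5%, difference 30.6 points. The same formula gives 78.2%; 74 patients would be needed for 80%.

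The range for missing as failure with 70 patients:

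| Missing per arm | Power |
|---|---|
| 5% | 81.8% |
| 10% | 78.2% |
| 15% | 74.5% |
| 20% | 70.5% |

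So the inflation from 62 to 70 matches exclusion, not the failure rule.

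**Step 3. Can the choice change the result?** The article gives no responder counts and no missing numbers beyond the 10% allowance. The tables below are therefore assumptions, with 7 of 70 outcomes missing. All p-values are two-sided chi-square without continuity correction.

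| Missing, A v B | All randomised, missing = failure | Missing excluded |
|---|---|---|
| 3 v 4 | 5/35 v 12/35: difference 20.0 points, p=0.051 | 5/32 v 12/31: difference 23.1 points, p=0.039 |
| 6 v 1 | 7/35 v 16/35: difference 25.7 points, p=0.022 | 7/29 v 16/34: difference 22.9 points, p=0.060 |
| 3 v 4 | 7/35 v 16/35: difference 25.7 points, p=0.022 | 7/32 v 16/31: difference 29.7 points, p=0.014 |
| 6 v 1 | 7/35 v 19/35: difference 34.3 points, p=0.003 | 7/29 v 19/34: difference 31.7 points, p=0.011 |

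The estimate moves in every row. Significance at 0.05 changes in the first two rows, in opposite directions, so neither rule is reliably the cautious one. It does not change in the third row, where missingness is near even, or in the fourth, where the effect is close to the planned one.

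**The case against.** The best defence is that the paragraph defining the remission rate is the more specific text. It fixes numerator, denominator and the handling of missing outcomes, and it promises the number missing by arm. If the earlier sentence means only that no model-based imputation is planned, the primary analysis is already all randomised patients with missing as failure. That narrows the ambiguity but does not remove it: it explains neither why sample-size inflation is offered in place of imputation nor why modified intention-to-treat is named for the primary analyses.

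Three stronger readings are tempting, and the article supports none of them.

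- *The exclusions undo the randomisation.* That follows only if the modified intention-to-treat reading governs. With all randomised in the denominator nobody is excluded, and the article gives no figure for patients who would be.
- *The denominator will be chosen after the data are seen.* The article describes itself as a brief outline and refers to a formal SAP, which is not shown and may settle the matter. A late choice is a risk, not something the article establishes.
- *The verdict is likely to flip.* The 6 v 1 split is lopsided. If 7 missing patients fell at random over 70, a split of at least 6 to 1 towards Arm A would have a probability of about 5%. Missingness may also be limited, because Trial outcomes says that week-24 assessments are still sought after removal or declined participation unless consent is withdrawn.

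The SAP cannot excuse the conflict itself, because the article states the incompatible rules rather than leaving one out.

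**Conclusion.** The point holds as an internal contradiction about the primary endpoint. Population, denominator and missing-data rule conflict within one section, and no reading satisfies all the sentences. The effect on the estimate was about 3 to 4 points in the tables tried. An effect on significance is confined to borderline results or unbalanced dropout. These sizes rest on assumed responder counts and on missing numbers set at the 10% planning allowance.

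The sample size arithmetic is correct but belongs to the exclusion rule. Under the failure rule, power at 10% missing is about 78% rather than about 81%. That shortfall is small, and it assumes missingness independent of outcome and planning rates that refer to assessed patients.

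**What to change.** State one rule, in the same words, in the protocol and the SAP:

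1. The primary analysis includes all randomised patients in their allocated arm, with a missing week-24 status scored as no remission. The paragraph defining the rate already says this.
2. Delete the sentence that rules out imputation and points to sample-size inflation, and stop naming modified intention-to-treat as the population for the primary analysis.
3. Label the modified intention-to-treat and complete-case analyses as sensitivity analyses. A tipping-point analysis is a useful option, because scoring missing as failure favours the arm with less dropout.
4. Align the Sample size calculation section. Say that 70 patients give about 78% power if 10% per arm are missing and counted as failures, or justify the number on that basis. Keeping 80% under the same assumptions would take 74 patients.

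The cost is a wording change and a restated power figure, with no new data. Recruitment is scheduled to last until September 2026, so the change should be made and dated before outcome data by arm are examined.
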